#### Internal pilot study to re-assess assumptions on variability and correlation

At both the first and second interim analyses, we will reassess the following assumptions used in sample calculations: within-subject correlation over time, mean # measurements per subject, control group proportions across stages. Reassessing these “nuisance” parameters will not affect the type I error but may result in increasing the maximum planned sample size. We will not reconsider the treatment effect of interest.

### Interim analysis

Interim analyses will be performed at each 25% of the planned enrollment using a group sequential design assessing the treatment effect on the primary outcome for efficacy and futility. We will use a gamma spending function with gamma parameters − 4 for efficacy and − 1 for futility. Stopping boundaries will be statistically non-binding; statistical accommodation for this option was made in the sample size calculations. The decision whether to stop a study at any interim analysis would be made by the DSMB, which would consider not only the statistical boundaries but other information as well. For example, if a futility or efficacy boundary was crossed at the first look, the DSMB might consider continuing the trial to obtain a more precise estimate of the treatment effect.

All data and results will be submitted to the data and safety monitoring board (DSMB) for review on an A versus B basis unless the DSMB requests to be unblinded. The DSMB is made up of physicians from multiple trial sites and a statistician (Additional file 5). The committee will assess any possible safety concerns, efficacy, and futility and advise if discontinuation is warranted and will meet at least yearly. DSMB members are independent from the sponsor and report to and communicate with the IRB and the steering committee.

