## Methods

### Trial design

PROTECT-2 is a parallel-group, unblinded multi-center randomized clinical trial that will assess whether IES combined with the standard of care (treatment) is superior to the standard of care alone (control). The trial is already IRB approved at all trial sites (US, Austria) and registered at ClinicalTrials.gov (NCT05085288). The SPIRIT checklist and figure for our proposal is provided in Fig. 1 and additional file 1. [12].

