### Randomization and blinding

Randomization sequences will be generated using the PLAN procedure in the SAS statistical software and will be stratified by clinical site and initial pressure injury stage at point of consent (stage I or II). Furthermore, random sized blocks will be used. Study personnel will randomize patients after enrollment via a central 24-h Interactive Web Randomization System (REDCap). This is an open label study, so no blinding is required. Randomization codes will be maintained until after all the data are collected and analyzed. The patient and study staff will be informed of the randomized allocation.

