#### Primary outcome

The primary outcome will be sacral and ischial pressure injury assessed with the SPI instrument score (range 0–4) over time. For the statistical analysis of clinical course, unstageable injuries will be assigned a score of 3 (equivalent to stage III injuries). For ulcers that progress to deep tissue injuries (DTI), these will be assigned a score of the previous ulcer stage plus one. If a patient experiences multiple sacral/ischial pressure injury simultaneously, the most severe injury will be used for analysis. The primary outcome will be based on the combined stage 1 and stage 2 ulcer types.

Patients will be assessed twice daily by the bedside nurse for pressure injury location and stage from study entry to discharge from the hospital or at least 30 days, whichever comes first. This is a standard wound care evaluation protocol for nursing. Wound care nursing specialist consultation staging will be used instead of bedside nursing staging should a discrepancy occur. If SPI scores are available after discharge and within the 30 days, those data will be included in the analyses as well, even if the SPI are healed or at the worst stage.

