### Trial organization

The Cleveland Clinic Department of Outcomes Research is the coordinating center for this trial and is responsible for the central randomization, trial database, data consistency checks, data analyses, and coordination of participating centers worldwide.

The group responsible for trial steering included the primary investigator from three of the research sites, a statistician from the coordinating center, two wound care nursing specialists from two of the research sites, and the chairmen of the Departments of Research from three of the research sites.

The endpoint adjudication committee members included the coordinating center PI, the statistician, and the chairman of the coordinating center research department.

The data management team included a statistician, a member of the database and data quality control arm of the coordinating center research department, and a research fellow. Day-to-day trial conduct is undertaken by research personnel to include fellows and nurses, the primary investigator from each site, two wound care nurses from the coordinating center, the database manager (weekly), and the statistician (weekly).

No stakeholder or public involvement group was utilized for the design of this trial.

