## Trial progress

This paper is based on the most recent version of the study protocol (i.e., v5.0, 2023-12-29). The first patient was randomized on June 6, 2022. As of December 30, 2023, we have recruited 176 patients across 3 centers in 2 countries. The first interim analysis based on recruitment is anticipated to be completed January 2024.

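### The DSMB physicians are drawn from the trial's own sites and independence is claimed only from the sponsor, so interim results by arm can reach physicians at enrolling institutions in an open-label trial

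*Protocol article*

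**What the plan says.** All of this is in the protocol article.

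- **Composition** (Interim analysis): "The DSMB is made up of physicians from multiple trial sites and a statistician (Additional file 5".
- **Independence and reporting line** (Interim analysis): "DSMB members are independent from the sponsor and report to and communicate with the IRB and the steering committee".
- **What the board sees** (Interim analysis): all data and results, "for review on an A versus B basis unless the DSMB requests to be unblinded". Looks take place at each quarter of planned enrollment. The boundaries are non-binding, and the board may weigh other information when it considers stopping.
- **Meaning of the term for sites** (Trial design): "The trial is already IRB approved at all trial sites (US, Austria".
- **Steering** (Trial organization): "The group responsible for trial steering included the primary investigator from three of the research sites". Research-department chairmen from three sites also belong to this group.
- **Blinding** (Randomization and blinding): "This is an open label study, so no blinding is required".
- **Outcome assessment** (Primary outcome): "Patients will be assessed twice daily by the bedside nurse for pressure injury location and stage". A wound-care specialist's staging replaces the nurse's where they differ.
- **Progress** (Trial progress): by 30 December 2023, "we have recruited 176 patients across 3 centers in 2 countries". The first interim analysis was expected to be completed in January 2024.

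**The concern.** A monitoring board has to see comparative results, so its members should be people who cannot affect the trial while they hold that knowledge. Here the article places the board's physicians at the trial's own sites and claims a different independence, from the sponsor, which does not address the point.

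This trial is more exposed than most. Nobody at the bedside is blinded, the primary outcome is a judgment of wound stage made by hospital staff, and co-treatment and discharge timing are also decided locally. If an interim trend became known at a site, it could affect who is approached for enrollment, how wounds are cared for and staged, and how consistently the device is used. The credibility of a decision to stop or continue is also at stake: because the boundaries are non-binding, that decision rests on the members' judgment.

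**Working it through.** The point is about governance, so the main check sets the statements side by side. The arithmetic only places the looks in time.

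**Step 1. Do the DSMB physicians come from the trial's own sites?** The composition sentence locates them at multiple trial sites. The Trial design section uses that term for the hospitals in the US and Austria where the trial has ethics approval. No passage gives it another meaning. The plain reading is yes.

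**Step 2. From whom is independence claimed?** The sentence names the sponsor only. Neither it nor the Discussion, which says that members were chosen for research expertise, mentions independence from sites, investigators or the steering group.

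**Step 3. How often, and when, does the board see results by arm?**

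- Planned enrollment (Abstract; Sample size considerations): 548. It reproduces from the article's inputs of 668 observations, 10 measurements per patient and ICC 0.8: 668 × (1 + 9 × 0.8) / 10 = 547.76, or 548.
- Interim looks: 0.25 × 548 = 137; 0.50 × 548 = 274; 0.75 × 548 = 411.
- Recruitment at the last report: 176, which is 39 beyond the first look and 274 − 176 = 98 short of the second.
- The sample-size section also mentions a maximum of about 1100, for which the first look would fall at 275. A first look in January 2024 with 176 recruited fits the 548 basis, which is assumed here.

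The gamma spending function with parameter −4 gives cumulative two-sided alpha α(t) = 0.05 × (1 − e^(4t)) / (1 − e^4):

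| Look | Patients | Cumulative alpha spent |
|---|---|---|
| 25% | 137 | 0.0016 |
| 50% | 274 | 0.0060 |
| 75% | 411 | 0.0178 |
| Final | 548 | 0.0500 |

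Little alpha is spent early, so only a strong effect would cross the efficacy boundary at the first looks. If neither boundary is crossed, or the board continues despite a crossing, enrollment and unblinded staging go on after members have seen results by arm. This can happen up to three times.

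**Step 4. Does the A-versus-B coding close the route?** Only partly. The board may ask for the code. Questionnaire items on the feeling of electric shock and on the skin of the device area (Exploratory outcomes) could also reveal which arm has the device.

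**Step 5. Is there a stated barrier between board and sites?** Members report to and communicate with a steering group that includes site investigators. The article does not say that results by arm are passed on, nor that they are withheld.

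**The case against.** The strongest reply is that the deciding facts lie in Additional file 5, which is not shown. Membership, conflict-of-interest rules and confidentiality terms may be set out there, and an article commonly leaves them to such a file. This stands as a limit on what can be concluded about individual members. It does not answer the composition sentence, which the article itself states and which needs correcting if the file says otherwise.

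Two further replies also stand. A board that reviews comparative data, or asks for the code, is doing its job; the weakness of the coding matters only because of where the members work. And a steering committee that receives DSMB advice is ordinary practice.

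Some stronger readings are tempting, but the document does not support them:

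- **That the stated independence is false.** What is stated is independence from the sponsor. A post at a trial site does not contradict that, and the text shown does not identify the sponsor, so the claim can be neither confirmed nor refuted.
- **That members are colleagues of those who enroll, treat and stage.** This is an inference from shared institutions. No passage says that a member is an investigator or works with a site team.
- **That at least two of three centers, and so about two-thirds of patients, are affected.** The three centers are those that had recruited by the end of 2023, not a full site list. The article elsewhere speaks of various centers and of participating centers worldwide. The fraction would also need even accrual, and it would still show no influence on care.
- **That members sit at the coordinating center.** No passage places one there.

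**Conclusion.** The concern holds in a limited form. As written, the plan draws its DSMB physicians from the trial's sites and claims the wrong kind of independence for the purpose. That gives interim results by arm a route to enrolling institutions, at up to three looks, in an open-label trial with a nurse-staged outcome and non-binding boundaries.

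The conclusion rests on reading the term for sites as the Trial design section uses it, and on Additional file 5 not contradicting the composition sentence. The resulting bias cannot be sized from the document, and it is not shown that any has occurred. No estimand, error rate, sample size or analysis changes. The case for acting is that the change is cheap and protects the credibility of any stopping decision.

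**What to change.** 1. In the Interim analysis section, state that DSMB members hold no post at a participating site and are independent of the investigators and the steering group, as well as of the sponsor.
2. Before the next look, replace any member who does not meet this with a physician from a non-participating hospital. If Additional file 5 shows that all members already meet it, correct the composition sentence instead.
3. State that the steering committee receives only a recommendation from the DSMB (continue, modify or stop), without data by arm.

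The board stays the same size, and the sample size and analysis are unaffected. The costs are the time to recruit and brief replacements and some loss of continuity. The first look was expected in January 2024; if it has been held, exposure at that look cannot be undone, but the looks at about 274 and 411 patients can still be protected if they have not yet taken place.

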### Sample size considerations

Sample size calculations are based on the primary outcome of pressure ulcer score (0–4), measured over time within a patient and assuming a statistical model (mixed effects ordinal regression) which accounts for the within-subject correlation over the repeated measurements. We designed the study to have 90% power at the 0.05 significance level to detect a treatment effect as large or larger than the effect seen in Table 1 (A) (for the combined starting stages I and II). Sample size was estimated based on applying a design effect to a standard 2-group comparison for independent data (i.e., the Wilcoxon Rank Sum test); it incorporates the number of measurements per patient (m) and an assumed intraclass correlation (ICC) to account for within-subject correlation (i.e., multiply standard sample size calculation by 1 + (m-1)ICC) [15].

**Table 1 Tab1:** Minimal clinically important differences in pressure ulcer score

**A. Combined stages I and II** ***N***** = 586 fixed, *****assuming single measurement***** per patient** ***N***** = 668 with interim analysis adjustment**	**Pressure ulcer score (row percent)**				
	**0**	**I**	**II**	**III**	**IV**
**Intervention**	**82.5**	**2.5**	**12.5**	**2.5**	**0**
**Control**	**72.5**	**2.5**	**15**	**5**	**5**

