#### Significance level

The significance level will be 0.05 for all hypothesis testing and will be controlled at 5% across any multiple comparisons using appropriate multiple testing procedures. Two-sided tests for superiority will be used throughout.

For the statistical analysis of clinical course, unstageable injuries will be assigned a score of 3 (equivalent to stage III injuries). If a patient experiences multiple sacral/ischial pressure injury simultaneously, the most severe injury will be used for analysis.

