#### Primary outcome analyses

We will assess the efficacy of an IES system added to the standard care versus standard wound care on sacral and ischial pressure injury scores measured over time using a generalized mixed effects ordinal regression cumulative logit model which considers treatment and time (categorical) as fixed effects and subject as a random effect and accounts for (1) the ordinal nature of the data and (2) the within-subject correlation over time. The model will allow differing number of measurements and lengths of follow-up for patients but will assume that shorter follow-up or dropout is largely at random and not due to either improvement or worsening of SPI symptoms. We will also assess the treatment-by-time interaction to assess whether the treatment effect is consistent over time. Given a significant interaction, we will assess the treatment effect at various time points, although the primary analysis will be the treatment effect collapsed over time.

Results will be reported as a proportional odds ratio which estimates the odds of an IES-treated patient having a higher (worse) score than a randomly chosen standard care patient. For example, an odds ratio of 0.6 would mean the treatment was associated with an estimated 40% lower odds of an EIS-treated patient having a higher score compared to standard care; correspondingly, a treated patient has a 40% higher odds of having a lower (better) score compared to a standard care patient.

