**C. Patients starting at stage II** ***N***** = 616 fixed (697 with interims)**					
	**0**	**I**	**II**	**III**	**IV**
**Intervention**	**80**	**0**	**17.5**	**2.5**	**0**
**Control**	**70**	**0**	**20**	**5**	**5**

Hypothetical percent in each pressure ulcer score category by treatment arm, for smallest clinically important effects: overall (A), for stage I (B), and stage II (C)

Table 2 gives total sample size for the combined stages in Table 1 (A), varying the number of measurements per subject (10, 20, 40) and varying ICC (0.2, 0.5, 0.8). The ICC is expected to be relatively high, so the recommended minimum sample size is 548 total (274/gp) for the overall treatment effect combining stages 1 and 2. However, since sufficient power is desired for each of the 2 starting strata, stage I and stage II, roughly the same sample size (548) should be achieved for each strata (see Table 2 for stage I and stage II strata). Therefore, a total maximum (accounting for interim analyses) sample size of approximately 1100 patients was recommended for this trial.

**Table 2 Tab2:** Sample size for varying # measurements and ICC. Data = *N* total. Starting with *N* = 668 total observations (Table 1 (A)), what is the required *N* subjects accounting for ICC and expected number of measurements/subject?

Patient sample	*N* measurements per patient	ICC		
		**.2**	**.5**	**.8**
**Combined stages **Table 1** (A) effect**	**10**	*188*	*368*	*548*
	**20**	*162*	*351*	*542*
	**40**	*148*	*344*	*538*
**Stage I start **Table 1** (B) effect**	**10**	174	342	510
	**20**	150	326	504
	**40**	138	318	500
**Stage II start **Table 1** (C) effect**	**10**	196	384	572
	**20**	168	366	564
	**40**	154	358	562

*N* = 668 assumed 1 measurement per patient (Table 1)

*ICC* intraclass correlation

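### The 90% power at 548 patients gives every assessment the Table 1(A) contrast, but that contrast is zero at entry and the primary test averages from entry, so 90% holds only if healing is fast

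*Protocol article*

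**What the plan says.** Under Sample size considerations, the article claims "90% power at the 0.05 significance level" and gives the aim as "to detect a treatment effect as large or larger than the effect seen in Table 1 (A"). Scores 0/I/II/III/IV there are 82.5/2.5/12.5/2.5/0% with intervention and 72.5/2.5/15/5/5% with control. No time point is attached to the table. The base calculation is a "standard 2-group comparison for independent data (i.e., the Wilcoxon Rank Sum test"), and the instruction for repeated measures is to "multiply standard sample size calculation by 1 + (m-1)ICC". The footnote to Table 2 confirms the starting point: N = "668 assumed 1 measurement per patient (Table 1"). With 10 measurements and an ICC of 0.8 this gives 548 in total.

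Four other parts of the article bear on this:

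- **Trial population:** each patient must have a stage 1 or 2 sacral or ischial injury; 548 is the minimum enrolment.
- **Primary outcome:** "Patients will be assessed twice daily by the bedside nurse for pressure injury location and stage from study entry".
- **Primary outcome analyses:** a cumulative-logit mixed model with treatment and categorical time as fixed effects and subject as a random effect, where "the primary analysis will be the treatment effect collapsed over time".
- **Internal pilot study:** control proportions, within-subject correlation and number of measurements are re-estimated at the first two interim analyses. The target effect is not.

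**The concern.** The design effect corrects for correlation between a patient's scores. It does not correct for a treatment contrast that starts at zero and grows. Randomized patients who all have an ulcer cannot show a 10-point difference in the share healed at the first assessment, and are unlikely to show it soon after. Those assessments still enter the time-collapsed odds ratio.

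At stake is how a neutral result is read. If 90% is quoted for a test that has materially less, a null finding, or a futility crossing at one of the interim looks, could be taken as well-powered evidence of no benefit.

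**Working it through.** **1. Reproduce the plan's figures.** Inputs: Table 1(A), two-sided alpha 0.05 (the Significance level section says "Two-sided tests for superiority will be used throughout"), 90% power, equal groups.

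- Probability that an intervention patient has the better score, ties counted half: θ = 0.556.
- Tie term: sum of cubed pooled proportions = 0.468.
- N = (1.960 + 1.282)² × (1 − 0.468) / [3 × (0.0562)²] ≈ 589, against 586 stated.
- Four looks with gamma spending of −4 and −1, non-binding, inflate N by about 1.136: 586 becomes about 666, against 668 stated.
- 668 × (1 + 9 × 0.8) / 10 = 547.8, against 548 stated.

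Simulating 548 patients with the Table 1(A) distribution at all 10 assessments and an ICC of 0.8 gives 90.0% group-sequential power. The arithmetic is sound; the question is the premise.

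**2. Could Table 1(A) be a time average?** With 10 assessments including entry, at most 9/10 = 90% of scores can be 0, even if everyone heals by the second assessment. An average of 82.5% requires every patient to heal, after on average no more than 100 − 82.5 = 17.5% of follow-up. At two scores a day, 10 assessments span about 5 days, and 0.175 × 5 ≈ 0.9 day. If some patients never heal, the others must heal faster still.

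**3. Rough illustration by the plan's own method.** Let a share w of assessments follow Table 1(A) and the rest stay at entry stage (assumed half stage I, half stage II). The 548 patients correspond to 586 in a fixed design.

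| w | θ | Power |
|---|---|---|
| 1.0 | 0.556 | 90% |
| 0.9 | 0.554 | 80% |
| 0.8 | 0.551 | 69% |
| 0.5 | 0.538 | 38% |

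This holds the ICC at 0.8. When scores change during follow-up the ICC falls: a simulation of the control arm gave a rank ICC of about 0.50, 0.55 and 0.69 for changes spread over all, the first half and the first fifth of follow-up. The table therefore shows the direction of the effect and overstates its size.

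**4. Simulation from entry stage.** Assumptions, not in the article: half of patients start at each stage, each changes once to an outcome drawn from Table 1(B) or (C), N = 548, 10 assessments. Two sets of mixed-model runs and two sets of rank-test runs were made.

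| Changes spread over | Ordinal mixed model | Rank test, unadjusted | Rank test, adjusted for entry stage |
|---|---|---|---|
| All of follow-up | 71% (final look); second set 63% group-sequential, 68% fixed-sample | 37%, 47% | 61% |
| First half | 93% (unconfirmed) | 75%, 79% | 81% |
| First quarter | not run | 81% | 84% |
| First fifth | 97% (unconfirmed) | 87% | not run |

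With 20 assessments, the 71% becomes 74%. The 93% and 97% come from one set of mixed-model runs. Attempts to confirm the mixed-model results for faster paths were numerically unstable, so those two figures carry less weight.

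**The case against.** **Table 1 is a hypothetical smallest important effect.** It may be meant as the average over time, and power is always conditional on the effect assumed. The text does not exclude this reading. A reader might infer that Table 1(A) can only describe a late time point; that goes too far. The time-average reading is implausible rather than impossible, given the healing speed in step 2.

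**No healing path is given, so no shortfall is proven.** This stands in part. A reader might infer that the trial has 38% or 71% power. The documents do not support any single figure: the first rests on a fixed ICC, the second on the slowest path. With early change, some results exceed 90%.

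**A mostly healed distribution is not itself the fault.** This is correct. With a constant odds ratio of about 0.56 at every assessment, a less healed control group needs fewer patients (about 400 to 470, against about 670 with the Table 1(A) control proportions). The cause is dilution of the contrast over time, and a constant odds ratio cannot hold at entry.

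**There are safeguards.** The internal pilot may raise the sample size, and a maximum of about 1100 is recommended. At 1100, rank-test power would be about 77% (unadjusted) to 89% (adjusted) on the slowest path and at least 96% if changes finish by half of follow-up. But the pilot leaves the target effect untouched and guarantees no increase, and 548 is the stated minimum to which the power claim is tied.

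**Handling of the entry score may be in an analysis plan not shown.** Agreed, and its absence here is no fault. The mismatch between the printed power calculation and the printed primary analysis remains.

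**Conclusion.** The concern holds in a limited form. The 90% at 548 is correct only if all assessments share the Table 1(A) contrast, which cannot be true at entry and is unlikely soon after. If healing and worsening spread over the whole of follow-up, power is well below 90% under every test tried. If they finish early, power is near 90%, from about 80% to above 90% depending on the test. The range rests on an assumed single change per patient and an even mix of entry stages. Patients who also have a higher-stage injury may enter with a score above 2, which does not alter the point. The plan should be changed, but the trial has not been shown to be underpowered.

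**What to change.** 1. State the day, or the averaging period, to which Table 1(A) refers.
2. Recompute power for the time-collapsed odds ratio by simulating the planned mixed model from entry stage, over a stated range of healing speeds and with the planned interim looks. Confirm that the model converges on these data.
3. Replace the 90% claim with the resulting figure or range, and use the same simulation when the internal pilot re-estimates its parameters.
4. Do not count the entry assessment as an outcome. Adjust for entry stage, which is already a stratification factor. In the paired rank-test runs this raised power from 47% to 61% on the slowest path and from 75% to 81% when changes finished by half of follow-up.

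The cost is one simulation study and revised sample-size and model wording. The downside is a stated power that may be lower and is given as a range. Restating it does not raise it; if the lower end is unacceptable, the sponsor would have to consider enrolling more than the minimum of 548.
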